### Qualitative analysis and rigor

2.10

The verbatim interview transcripts, field notes from observations, and field notes from informal conversations, will be analyzed separately using inductive thematic analysis, through the following steps: 1) a holistic approach where transcripts are read several times to obtain an overall understanding of the content; 2) a selective approach where meaningful units are identified; 3) a detailed approach where meaningful units are coded; and 4) meaningful units and codes are summarized into essential themes (32, 33). The credibility of the qualitative findings will be ensured through prolonged engagement in the field, an active search for “negative cases”, and investigator triangulation, with more than one researcher conducting the interviews, observations, and analyses (34). Transferability is ensured by including observations and interviews from many participants, thereby broadening perspectives and experiences. Thick descriptions will be included with direct text passages from observations and direct quotes from interviews, allowing the reader to judge the fittingness of the findings (34, 35).

### Data management

2.11

All quantitative data are collected in paper form and then manually entered in a secure electronic database (REDCap) by a member of the project team. Paper forms are stored in a locked cabinet at the trial site. As this process can produce data management errors, the data will be cross-checked independently by two members of the project team to ensure its quality. Qualitative data as interview files and observational field notes will be stored in a secure electronic folder and original interview files will be deleted from the voice recorder after transfer.

## Discussion

3

This protocol reflects the choices made when designing the SPARK trial. It considers the expected challenges, strengths, and dilemmas of conducting a hospital- and home-based intervention for preschool children undergoing intensive cancer treatment, with parents as an important stakeholder, and ensuring viable outcome measures.

### The intervention design

3.1

Our results from the previous RePlay trial revealed considerable variability in adherence (0%–95%), which was attributed to logistical challenges, flexibility, and the availability of facilities (10). To address these issues in the SPARK trial, we propose a more flexible intervention design that offers the intervention daily, at the ward, near the patients. This approach is expected to enhance adherence by making the intervention more accessible and convenient, as seen in previous physical activity intervention trials for children with cancer (36, 37). Furthermore, preschoolers should be physically active or participate in active play as much as possible every day, with minimal sedentary activity (2); thus, offering the intervention daily will increase their opportunities to be physically active at the hospital. However, there is a shift towards more home-based treatment to reduce hospital stays and the interruption of family routines and normalcy (38, 39). This calls for effective solutions to support parents in physical activity with their child at home. The SPARK trial is designed with an intervention group that includes additional components of a parent educational program and online supervised group-based social and physical activity at home. The online sessions provide children and parents with regular opportunities for physical activity at home. While online physical activity has proven effective for older children (age 4–18 years) with cancer (40), engaging younger children through a screen may be challenging. Therefore, the role of parents is crucial in these sessions, which are designed to be more interactive and guided rather than instructor-led activities. Additionally, the parent educational program is based on the premise that parents who are more knowledgeable about physical activity tend to have more physically active children (41, 42). Still, developing such a program requires careful consideration. Previous research indicates that parents often feel overwhelmed by the numerous treatment-related responsibilities and tasks they must manage at home (7, 43). Results from the RePlay trial also highlighted that parents appreciated having some of the responsibility taken off their shoulders and valued the shared responsibility of their child's physical activity (12). Conversely, parents also expressed uncertainty about how to engage their children in physical activity at home, and they found the structured active play sessions at the hospital to be a valuable source of inspiration (12). In developing the parent educational program, we made deliberate decisions regarding the timing and length of the educational sessions and the amount of information provided to ensure it was manageable for the parents. We want to begin the intervention as early as possible, as research has shown that physical side-effects are already present within the first month of treatment (44), which is why we include the families within the first 14 days of treatment. However, the timing of the parent educational program is planned for the first two months of treatment to accommodate the treatment-related information load that parents will experience during the first month. As part of the normal interactions with the families throughout the intervention, parents may ask for additional information or have questions. Interacting and answering parents’ additional questions is an unavoidable part of the intervention, but it is not structured or approached systematically, and we do not offer additional educational sessions. Additionally, to ensure a feasible design, both the parent educational program and the online supervised structured active play were developed with input from parents of preschool children in active treatment and tested before the onset of the randomized controlled trial.

When deciding on outcome measures in the SPARK trial, we chose to limit the included outcomes to the PDMS-3 in the assessment of the children. This decision was based on feasibility results from the RePlay trial, showing that many factors influenced the feasibility of outcome assessment in the children throughout the treatment trajectory, including health-related issues, pain, and unwillingness (10). Additionally, the length of the outcome assessment, with the inclusion of more outcomes, some of which were not suitable for the age group, contributed to the complexity (10). Simplifying the outcome measures to focus on the most essential aspect of gross motor function may help improve completion rates.

### Strengths and limitations

3.2

The variability of the intervention can be viewed as both a strength and a limitation. Due to the side-effects of medical treatment—particularly chemotherapy and corticosteroids—the children's physical capacities fluctuate substantially from day to day. Consequently, the activities must be continuously tailored to each child's current condition to align the daily capabilities with the intended motor challenge level. As a result, the actual exposure to the intervention will vary between participants in terms of duration, content, and intensity, and therefore lacks complete uniformity. However, this variability reflects an unavoidable premise of exercising during childhood cancer treatment. Importantly, the intervention is structured within a well-defined and previously tested framework (the RePlay Model) (15), developed and evaluated in the same study population. This ensures the highest possible degree of standardization while maintaining flexibility for individual adjustments. To evaluate the feasibility and quality of the intervention delivery, we will assess adherence and conduct semi-structured interviews.

A challenge in the present study is the heterogeneity of the participant group, as we include all diagnoses. This increases the complexity of data analysis and may limit the generalizability of the results, particularly when evaluating the overall effect of the intervention across diverse clinical profiles with variations in symptoms and treatment protocols. To address this, we have implemented stratification in the randomization process across diagnostic groups. In contrast, including children with all diagnoses provides a broader insight into the entire patient population and enables future subgroup analyses that may inform more targeted approaches. From an ethical perspective, this is a strength because it ensures that every child has access to the intervention, upholding the principle of equity in healthcare by removing barriers to participation.

The study design includes two active intervention groups, which can be regarded as both a strength and a limitation. Because both study arms receive active interventions, the contrast between groups may be reduced. This overlap in intervention components or mechanisms of action can attenuate observed between-group differences and may lead to an underestimation of the true intervention effect. We expect the additional intervention components to be essential, particularly given that families are spending more time at home and that the intervention is tailored to this context. On the contrary, these components have not been previously tested or evaluated in a trial, and despite a small test period prior to the SPARK RCT, their feasibility remains unknown. Still, we expect the anticipated increase in gross motor function of 25% to be attainable as this responds to an increase in standard score by five “points” across all three subtests. Additionally, the design ensures that the social element of the intervention is supported, as all children in the ward can participate in the play activities at the hospital.

As the literature and evidence are still limited on physical activity interventions and initiatives specifically for preschoolers, we chose to include numerous feasibility and evaluation measures and qualitative explorations to ensure that future interventions and initiatives can be tailored to preschoolers’ and their parents’ needs. Qualitative research within a randomized controlled trial can be a strength as it provides a comprehensive understanding of the intervention from the user's perspective (45). This broadens our understanding and allows us to explore other impacts and new questions that arise.

This protocol outlines a clinical trial designed to generate data on the effect of a multicomponent intervention comprising in-hospital supervised group-based social and physical activity, a parent educational program, and at-home online supervised group-based social and physical activity compared with a single-component, involving only in-hospital supervised group-based social and physical activity In addition to evaluating outcomes, the trial will explore the perspectives and experiences of both children and their parents. The results from the SPARK trial are expected to provide valuable evidence for the emerging yet under-researched field of rehabilitation in preschool-aged children undergoing cancer treatment, thereby advancing the development of best practices in this area—potentially transforming rehabilitation in preschoolers during cancer treatment.

## Ethics and dissemination

4

The SPARK trial adheres to the ethical research principles outlined in the Declaration of Helsinki. The study has been peer-reviewed and approved by the National Committee on Health Ethics Research through the Regional Research Ethics Committee in the Capital Region of Denmark (jr.nr.: H-25047770, and data handling is approved by the Danish Data Protection Agency (jr. nr.: p-2024-17472). Written informed consent is obtained from parents prior to their inclusion in the trial. Parents are informed that participation is voluntary and that they may withdraw their consent at any time, with no consequences for their child's further treatment. All personal or descriptive data is pseudonymized and will be presented in clusters. The interviews and observational field notes are pseudonymized.

### Safety and adverse events

4.1

Our previous findings from the Rehabilitation including structured active play for preschoolers with cancer (RePlay) trial show that physical activity, such as structured active play and physical assessment, was found safe for preschool children with cancer, regardless of diagnosis (10). Nevertheless, all adverse events, defined as unintended negative consequences experienced during the structured active play sessions and gross motor function assessments are documented, despite the possibility of a causal relationship between the intervention and usual care (31). In relation to daily inclusion safety criteria for physical activity, data on hemoglobin level, platelet and leukocyte counts, temperature, and signs and symptoms of infection are obtained from the treating physician and nurse. As the trial is perceived as a low-risk trial, there is no data monitoring committee, and the principal investigator is responsible for monitoring the safety of the trial.

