### Intervention

2.6

The SPARK trial consists of two intervention groups. Both groups will receive usual care which include occupational therapy and physiotherapy if needed. Intervention group (a) includes nine months of supervised group-based social and physical activity at the hospital conducted as structured active play sessions. Intervention group (b) comprises a nine-month program of supervised group-based social and physical activity at the hospital, conducted as structured active play sessions, combined with a parent educational program, and supervised group-based social and physical activity delivered online for implementation at home. The different intervention components are described in detail below.

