#### Parent educational program

2.6.2

The parent educational program consists of two 30–60 min educational sessions within the first two months of the child's treatment trajectory. The sessions aim to provide parents with the knowledge and skills to facilitate structured, active play at home. Session 1 provides general information on gross motor function development, common physical side effects of cancer treatment, and the importance of physical activity. Session 2 includes an interactive introduction to structured active play and the RePlay Model, including the inspiration for active play activities that can be done at home to challenge different gross motor skills. The parents will receive practical materials on gross motor development stages and skills, as well as descriptions and access to videos of active play activities that target gross motor functions. The parents are encouraged to facilitate and partake in structured active play with their child daily when they are not at the hospital, and to participate in the online supervised group sessions.

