#### Online supervised group-based social and physical activity at home

2.6.3

To support the parents in facilitating structured active play at home, we will provide online supervised group-based social and physical activity at home. These sessions will be available daily during weekdays (i.e., Monday–Friday). Here, the families can log on and have a healthcare professional (i.e., an exercise professional or physiotherapist) guide them through active play activities. The online supervised session requires parents to be the main facilitators in their home, guided by a healthcare professional who will initiate the session with a ritual and a familiar activity, as described above, and conclude it with a ritual. To accommodate families who are unable to join the online supervised sessions due to, for example, logistical constraints, they will have access to pre-recorded sessions they can follow at home at a time convenient for them. The online supervised group-based sessions serve as a supporting element for parents, providing them with an opportunity to systemize structured active play at home.

Each family will receive basic essential home-based active play equipment (e.g., bean bags, balls, bingo games, items for an obstacle course) for the online sessions. The sessions will be conducted through video connections (Teams or Skype).

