**QUALITATIVE EXPLORATION:**						
Interview						
Informal conversations						
Observation						

TTI, treatment initiation, T0 =  + 1–14 days after TTI (Baseline), T0^1^ = +1–14 days after TTI, T1 = 6 months (±14 days) after TTI, T2 = 9 months (±14 days) after TTI (post-intervention, primary end-point), T3 = 12 months (±14 days) after TTI.

^a^
Intervention group (a) and (b).

^b^
Only intervention group (b).

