### Statistical analysis

2.9

The primary outcome [gross motor sum of scaled scores from the three subtests (i.e., body control, body transport, and object control) of the PDMS-3] will be analyzed using analysis of covariance (ANCOVA) models with the residual variance depending on the group [intervention group (a) and intervention group (b)]. To investigate whether the impact of adjusting for the differences between the two groups could result from differences in age, diagnosis, and time since diagnosis, the groups will be compared in three different models: 1) a raw model without any adjustments, 2) a model further adjusted for diagnosis, and 3) time since diagnosis. The secondary outcome of the PEDI will be analyzed using a similar model. The Multiple-Choice Assessment will be analyzed using a Linear Mixed model to investigate post-intervention knowledge between parents in intervention group (a) and intervention group (b) while adjusting for baseline scores. Secondary analyses include within-group changes pre- and post-intervention, analyzed using paired *t*-tests. An alpha level of 0.05 will be considered significant. Descriptive statistics will be used to summarize feasibility outcomes (i.e., acceptance, attrition, completion, adherence, adverse events, and the parent evaluation survey).

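### Adverse events are counted only in play sessions and motor tests, and only group (b) has such sessions at home, so total counts by arm are not like for like

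*Protocol article*

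**What the plan says.** Section 4.1 (Safety and adverse events) defines adverse events as those "defined as unintended negative consequences experienced during the structured active play sessions and gross motor function assessments are documented", and adds that this is done "despite the possibility of a causal relationship between the intervention and usual care". I read this as recording events whatever their cause, but only inside that window. Section 2.7.4.3 (Feasibility) adds three grades of severity and no wider window.

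The arms differ in how much of their time falls inside the window:

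- Section 2.6 (Intervention): "Intervention group (a) includes nine months of supervised group-based social and physical activity at the hospital conducted as structured active play sessions". Group (a) has no home component.
- Section 2.6.3 (online activity, group (b) only according to the footnote to Table 1): live sessions are offered every weekday. For families who cannot join, "they will have access to pre-recorded sessions they can follow at home at a time convenient for them".
- Section 2.6.2 (parent educational program, also group (b) only): "The parents are encouraged to facilitate and partake in structured active play with their child daily when they are not at the hospital".

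Section 2.9 (Statistical analysis) plans descriptive statistics for the feasibility outcomes, listed as "acceptance, attrition, completion, adherence, adverse events, and the parent evaluation survey".

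**The concern.** The randomised contrast is the added package of parent education and play at home. The window for counting harm widens with that same package. A fall at home in group (a) is outside the definition. A similar fall in group (b) is inside it if it happens in a home session, provided someone reports it. A difference in totals can therefore come from the definition and from reporting as well as from risk.

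This matters more than usual for three reasons. Section 3.2 says that the added components have not been tested in a trial before. The reassurance on safety in section 4.1 comes from RePlay, which the Introduction describes as supervised activity. There is no data monitoring committee. The adverse event summary is thus a main source for a reader who asks whether adding home play is safe.

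**Working it through.** The plan states no harm figure, so there is none to reproduce. The check sets each setting against the definition in section 4.1.

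| Setting | Group (a) | Group (b) | Inside the definition? |
|---|---|---|---|
| Hospital sessions (2.6.1) | yes | yes | yes, same terms in both arms |
| PDMS-3 assessments (Table 1) | yes | yes | yes, same terms in both arms |
| Live online sessions at home (2.6.3) | no | yes | yes; a professional watches by video |
| Pre-recorded sessions at home (2.6.3) | no | yes | the article calls them sessions; no professional is present |
| Parent-led play at home (2.6.2) | no | encouraged daily | unclear; the article does not call it a session |
| Other activity at home | yes | yes | no |

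The first two rows can be compared between arms. The next three add countable time in group (b) only. The last row is uncounted in both arms, and it holds all of group (a)'s active time at home.

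**Illustration, with assumed inputs.** The article gives no attendance and no event rates. Assume:

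- 40 hospital sessions per child in each arm;
- M home sessions per child in (b);
- the same event rate r per session in both settings;
- a fraction f of events in home sessions reported.

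Then the recorded count per child is 40r in (a) and (40 + fM)r in (b), so

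recorded ratio (b):(a) = (40 + fM)/40.

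| M | f = 0 | f = 0.5 | f = 1 |
|---|---|---|---|
| 20 | 1.0 | 1.25 | 1.5 |
| 40 | 1.0 | 1.5 | 2.0 |
| 80 | 1.0 | 2.0 | 3.0 |

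Now take M = 40 and compare two possible truths:

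1. Children in (a) have no events at home. The true ratio is (40 + 40)/40 = 2.0. A recorded 2.0 is correct, and anything lower is under-capture in (b).
2. Children in (a) have as many events in ordinary home activity as children in (b) have in home sessions (40r each), and (b) has no others. The true ratio is (40 + 40)/(40 + 40) = 1.0. A recorded 2.0 is then a false excess, because (a)'s home events are left out by definition.

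The recorded ratio runs from 1.0 to 2.0 in both cases. It cannot tell the two truths apart, and that is the defect. The values themselves are not estimates. Live online sessions offer about 5 × 39 = 195 weekday slots over nine months, but that is availability rather than attendance; section 3.1 reports adherence from 0% to 95% in RePlay.

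**The case against.** A reader might infer that harm cannot be compared between the arms at all. The article does not support that. Hospital sessions and PDMS-3 assessments come under one definition on the same terms in both arms. Section 2.7.4.3 also assesses adherence for each intervention component, which should supply denominators for events per session attended.

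A reader might also infer that twice as many recorded events in (b) would be an artefact. That follows only if group (a) has home events that go uncounted (case 2 above). If it has none, the higher count is real, and the only error is under-capture in (b).

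Further points for the plan:

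- Safety is not among the study aims in section 1.1. Adverse events are a descriptive feasibility outcome, and a session-bound definition suits the question of whether sessions and tests can be delivered safely. This stands: no stated analysis is invalidated. A descriptive table by arm will still be read as comparative safety.
- Whether parent-led play counts as a session is not settled. This stands too, and the point does not need it, because live online and pre-recorded sessions already create the difference.
- Parents are present at home and could report events, and the reporting route may be in the full protocol. The adverse event row of Table 1 cannot be read in the text available. So I do not claim that home events in (b) will be missed. A reporting route for (b) would still give group (a) no countable time at home under the definition as printed.

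**Conclusion.** The point holds in a limited form. The definition in section 4.1 ties the counting of harm to an exposure that differs by arm. Total adverse event counts by arm are therefore not like for like, and the net harm of adding the home components cannot be estimated from them. Events in hospital sessions and motor assessments remain comparable.

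The direction of the distortion is open: more countable time raises the count in (b), and unreported home events lower it. Its size cannot be computed from the article, and the ratios above rest wholly on assumed attendance, equal risk per session and assumed reporting. The primary outcome and its analysis are untouched.

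**What to change.** 1. Report session-related events by setting (hospital, live online, pre-recorded or parent-led at home) per session attended. State whether parent-led play counts as a session. Where attendance at unsupervised play is not recorded, give the number of events without a rate. State that total counts by arm are not a measure of comparative safety.
2. At the PEDI interviews already held in both arms at T1, T2 and T3, ask all parents the same question about events during any physical activity, at home or in hospital, since the last assessment. Set a severity threshold in advance (for example, an event that led to medical contact) so that ordinary tumbles are left out. Record place and supervision. Summarise children with at least one such event by arm; T1 and T2 together cover the nine-month intervention and T3 the follow-up.

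The cost is one item on an existing interview form and one more descriptive table, with no added visits. The weakness is recall over up to six months (T0 to T1) by unblinded parents. Recall may also differ by arm, because only group (b) parents are taught about physical side effects and motor development. The severity threshold limits this bias but does not remove it, and the report should say so.
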